# Effect of multidisciplinary intensive targeted care in improving diabetes mellitus outcomes: a randomized controlled pilot study – the Integrated Diabetes Education, Awareness and Lifestyle modification in Singapore (IDEALS) Program

**DOI:** 10.1186/s13063-019-3601-3

**Published:** 2019-09-02

**Keywords:** Diabetes mellitus, Multidisciplinary care, Patient empowerment, Microvascular complications, Macrovascular complications, Atherosclerosis

## Abstract

**Background:**

There is a global pandemic of type 2 diabetes mellitus (T2DM), especially in Asia. Singapore has a prevalence of T2DM at 10.5%, which is higher than the world average of 8.8%. Multiple studies have shown that multidisciplinary, team-based, coordinated care has been associated with improved measures of quality care and reduced healthcare utilization. Patients with poor glycemic control and nephropathy are at the highest risk of developing cardiovascular complications and renal failure. In this study, we aimed to investigate the impact of intensive multidisciplinary diabetes mellitus care with patient empowerment versus routine clinical care on the rate of progression of micro and macrovascular complications and peripheral atherosclerotic burden, as measured by changes in femoral intima-media thickness (IMT) in patients with persistently elevated HbA1c and nephropathy.

**Methods:**

The study is a single-center randomized controlled trial (RCT) with two study arms - intensive diabetes mellitus care versus routine clinical care. Patients in the intensive arm will receive care from a multidisciplinary team consisting of an endocrinologist, diabetes nurse educator, dietitian, renal pharmacist and medical social worker for counselling. In addition, patients will be provided with tools for self-care empowerment such as glucometers, blood pressure monitors and android tablets to facilitate care, monitoring and education. Patients in the routine clinical care arm will receive standard clinical care. Follow up (FU) will be for 3 years. Primary outcomes include cardiovascular events, rate of progression of nephropathy and development of end-stage renal disease. Secondary endpoints include the proportions of patients with documented improved control of cardiovascular risk factors (HbA1c, blood pressure, low density lipoprotein-C (LDL-C), reduction in body weight), frequency of hypoglycemia, hospitalization days and changes in femoral IMT. We will also examine the prevalence of peripheral atherosclerosis and the predictive value and usability of lower extremity arterial ultrasound to predict cardio-cerebrovascular events, amputation and peripheral intervention.

**Discussion:**

Diabetes mellitus carries significant healthcare costs. Patients with poor glycemic control and nephropathy are at highest risk of developing cardiovascular complications and renal failure. Intensive diabetes mellitus care with patient empowerment may lead to sustained glycemic control, reduction of clinical complications and progression of nephropathy, and incidence of cardiovascular complications.

**Trial registration:**

ClinicalTrials.gov, NCT03413215. Registered on 29 January 2019.

**Electronic supplementary material:**

The online version of this article (10.1186/s13063-019-3601-3) contains supplementary material, which is available to authorized users.

## Introduction

### Background

The number of individuals with type 2 diabetes mellitus (T2DM) in Singapore, a Southeast Asian city-state with a population of 6.5 million, is estimated to grow from 400,000 to 670,000 by 2030 and to an alarming 1.0 million by 2050 with the continuing rise in the prevalence of obesity [1]. Total economic costs per working-age patient with T2DM in 2010 were estimated to be US$5,646, with total economic costs of US$787 million; this is estimated to rise to US$7,791 per patient and total economic costs of US$1,867 million by 2050 [2]. The presence of complications and need for inpatient care are major contributors to these increasing costs. Diabetic nephropathy is a major cause of morbidity and mortality. Asian ethnicity, uncontrolled hypertension and proteinuria are major risk factors for progression to end-stage renal failure [3]. Control of multiple risk factors, as in the Steno-2 study [4], has been shown to improve cardiovascular outcomes, increase the length of time free from incident cardiovascular disease, reduce the risk of death from all causes and reduce the progression of nephropathy as measured by worsening proteinuria, glomerular filtration rate (GFR) and serum creatinine. Previous trials have also suggested the utility of the chronic care model [5], structured recall [6], regular nurse contact [7], technology-enabled diabetes self-management education and support [8, 9] and a multifaceted approach in dealing with diabetes mellitus [6]. While most researchers have agreed that good glycemic outcomes are achievable through committing to appropriate intensive therapy and a team approach [10], there are multiple barriers to the implementation of quality diabetes mellitus care. In particular, barriers to good diabetes mellitus care can include the absence of a system to prioritize clinical resources for patients who require more intensive management, inadequate self-empowerment of patients, inadequate use of effective behavioral modification techniques, ineffective use of technology to enable diabetes self-management education and support and the need to self-fund glucose monitoring devices and monitoring and treatment consumables.

Accordingly, we aim to find out whether stratifying patients according to their risk of developing diabetic complications, and channeling purposefully structured clinical resources to high-risk patients will be more effective than usual care in controlling diabetes mellitus and cardiovascular risk factors and in reducing clinical event rates. We plan to structure clinical resources such that these patients will have accessibility to interdisciplinary team clinic consultations, interspersed with remote follow up of their conditions by diabetes nurse educators (DNEs). The use of messaging systems, a diabetes-specific smartphone application and smart tablets with diabetes self-management educational material will be individualized for patients, according to their preferences for communication and their technological literacy. The aim is to test whether these changes to the diabetes healthcare system will improve outcomes, yet remain sustainable in the current climate of heavy clinical workloads.

Diabetic macrovascular disease, manifested by accelerated atherosclerosis, and its complications are the leading causes of morbidity and mortality in patients with T2DM. Individuals with diabetes mellitus have twofold to fourfold higher peripheral rates of arterial disease and an approximately 15 times greater rate of lower extremity amputations [11]. At present, atherosclerotic lesions in the carotid arteries detected by ultrasound appear to represent total atherosclerotic burden [12] but this has been found to be only weakly related to plaque burden in other peripheral arteries [13]. Compared with carotid arterial plaques, the association between lower extremity atherosclerosis and general atherosclerosis has received much less attention. Our research aims to measure changes in femoral intima-media thickness (IMT) in high-risk patients with diabetes mellitus in response to intensive intervention, and investigate whether imaging to determine peripheral atheroma burden can help in predicting and preventing urgent and emergent peripheral vascular disease intervention.

## Methods

### Trial design

This is a single-center, randomized controlled trial of intensive diabetes mellitus care with patient empowerment versus routine clinical care.

### Aims and hypotheses

#### Main hypothesis

Intensive diabetes mellitus care involving the following strategies will be more effective than usual care in controlling diabetes mellitus, controlling multiple cardiovascular risk factors, slowing down the progression of nephropathy and peripheral atherosclerosis, reducing clinical event rates and decreasing the visits to specialist clinics and admissions to hospital for diabetes-related complications:
Channelling patients at high risk of developing diabetic complications to interdisciplinary team clinic consultationsActive counselling and teaching of self-care skills by allied health professionals (DNEs, medical social workers (MSWs), pharmacists)Closer, remote follow-up via telephone aided by simple technology to facilitate diabetes self-management education and support by the DNE and MSW between clinic visits

#### Secondary hypotheses and objectives

We will be examining the prevalence of peripheral atherosclerosis and the value of lower extremity arterial ultrasound in predicting cardio-cerebrovascular events and/or amputation, and in reducing the risk of hospital admissions for critical limb ischemia.

### Study population

Patients seen by endocrinologists for T2DM management at a regional hospital diabetes outpatient clinic in Singapore will be screened for eligibility for the study.

### Eligibility criteria

Patients will be considered eligible for the study if they fulfil the following criteria:
Aged 21–70 yearsPoorly controlled T2DM as defined by HbA1c ≥ 9%Nephropathy as defined by estimated GFR (eGFR) 30–60 ml/min and/or proteinuria classified as urine protein > 0.5 g/day and/or urine albumin:creatinine ratio (ACR) >30 mg/mmol on two consecutive measurements 3 months apart

Patients will be excluded from study participation if any of the following criteria are present:
Type 1 diabetes mellitus defined as a history of ketosis at diagnosis (acute symptoms with heavy ketonuria (urine value > 3+) or ketoacidosis) or continuous requirement of insulin within 1 year of diagnosis.Psychiatric conditions being treated by medications that adversely affect patients’ weight and stability of their mental health.Patients on weight loss medications or have had bariatric surgery, which may affect their mental health and compliance with dietary advice.Life expectancy < 12 months due to advanced cancer or other life-threatening conditions, such that they will not be able to perform self-care or complete 3 years of follow-up.Pregnant or lactating patients.

Patients will be withdrawn from the study if any of the following criteria apply:
The patient withdraws consentThe patient is no longer able to participate or the investigator, in discussion with the patient’s attending physician(s), decides to terminate participation on medical groundsThe patient becomes pregnant during the study

There will be no participant replacement in the study if a participant withdraws.

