#### Primary endpoints

The primary outcome measures are (1) rate of deterioration of chronic kidney disease (rate of decline of eGFR or worsening of proteinuria) or development of end-stage renal disease, whichever events happen and (2) cardiovascular events (composite events of acute myocardial infarction, revascularization procedures, heart failure, unstable angina, arrhythmia, stroke, transient ischemic attacks requiring hospital admissions) and related death, whichever events happen.

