### Sample size

The proposed sample size of 25 participants in each group is adequate to estimate the mean of the eGFR between the two groups of participants, effect size (2.5-unit difference) using the *t* test (two-tailed alpha = 0.05 with statistical power of 0.80).

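### Patients already at end-stage renal disease are not excluded, although developing it is a component of the renal primary endpoint

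*Protocol article*

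**What the plan says.** Under Eligibility criteria, the protocol article requires nephropathy, which it defines by three alternatives: "estimated GFR (eGFR) 30–60 ml/min and/or proteinuria classified as urine protein > 0.5 g/day and/or urine albumin:creatinine ratio (ACR) >30 mg/mmol". The alternatives are joined by and/or, so meeting one is enough. The eGFR range belongs to the first alternative only. The ACR alternative reads "and/or urine albumin:creatinine ratio (ACR) >30 mg/mmol on two consecutive measurements 3 months apart" and carries no eGFR limit.

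The same section lists five exclusions: type 1 diabetes, certain treated psychiatric conditions, weight-loss drugs or bariatric surgery, short life expectancy, and pregnancy or lactation. The nearest to a renal exclusion is "Life expectancy < 12 months due to advanced cancer or other life-threatening conditions", which is not an ESRD criterion. Study population adds no renal limit; it names only "Patients seen by endocrinologists for T2DM management at a regional hospital diabetes outpatient clinic in Singapore".

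Under Primary endpoints, the first primary outcome is the rate of deterioration of chronic kidney disease (eGFR decline or worsening proteinuria) "or development of end-stage renal disease, whichever events happen". The second is a composite of cardiovascular events and related death.

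**The concern.** An incidence endpoint can be read only in patients who are free of the event when they are randomised. Here the entry rule admits patients who may already have it. Someone with heavy proteinuria who is already at ESRD meets the nephropathy criterion and none of the listed exclusions. After randomisation that patient cannot develop ESRD and has little or no eGFR decline left to slow, whatever the arm. Statistical methods specifies an intention-to-treat analysis, so the patient stays in the renal comparison. With 25 patients per arm, each such patient is 1/25 = 4% of an arm.

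The eGFR criterion is also unclear in itself. A patient below 30 ml/min without proteinuria is ineligible, but a patient at the same eGFR with proteinuria is eligible. The reader cannot tell whether 30 was meant as a floor for everyone or only as the lower edge of one route.

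**Working it through.** **Step 1: who can enter.** No figure in the plan decides this; it follows from reading the sections together.

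| Question | Protocol article | Result |
|---|---|---|
| Must eGFR be 30–60 ml/min? | Eligibility criteria: alternatives joined by and/or | No, only on the eGFR route |
| Does another route carry an eGFR limit? | Eligibility criteria: proteinuria and ACR routes | No |
| Does an exclusion name ESRD, dialysis or transplant? | Eligibility criteria: five exclusions | No |
| Does the source population exclude them? | Study population: endocrinology outpatients | No |
| Is developing ESRD part of a primary endpoint? | Primary endpoints: first primary | Yes |

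A proteinuric patient at ESRD is therefore eligible and cannot have one of the events being counted.

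**Step 2: how much it matters.** From the document: n = 25 per arm (Randomization). Assumed, because the article gives no renal event risks: true risks of 30% (standard care) and 15% (intensive) in patients at risk. Also assumed: k patients already at ESRD in each arm, with k = 0, 1 or 2, counted as non-events because the endpoint is development of ESRD.

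Fraction at risk: f = (25 − k)/25. Observed risks: 30% × f and 15% × f.

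| k per arm | f | Standard care | Intensive | Risk difference | Relative risk |
|---|---|---|---|---|---|
| 0 | 1.00 | 30.0% | 15.0% | 15.0 points | 0.50 |
| 1 | 0.96 | 28.8% | 14.4% | 14.4 points | 0.50 |
| 2 | 0.92 | 27.6% | 13.8% | 13.8 points | 0.50 |

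The factor f cancels in the ratio, so the relative risk does not move when k is equal in both arms.

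**Step 3: precision.** With expected events a = 0.30(25 − k) and b = 0.15(25 − k), the standard error of the log relative risk is √(1/a + 1/b − 2/25).

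- k = 0: a = 7.5, b = 3.75; √(0.1333 + 0.2667 − 0.08) = 0.566
- k = 1: a = 7.2, b = 3.6; √(0.1389 + 0.2778 − 0.08) = 0.580
- k = 2: a = 6.9, b = 3.45; √(0.1449 + 0.2899 − 0.08) = 0.596

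The standard error rises by about 3% (0.580/0.566) to 5% (0.596/0.566).

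**Step 4: unequal numbers.** Equal k holds only on average. If two such patients fell in one arm and none in the other, the observed relative risk would be 15/27.6 = 0.54 (both in standard care) or 13.8/30 = 0.46 (both in the intensive arm). This is chance imbalance and can go either way; it is not a systematic bias.

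**The case against.** The strongest reply is that the point is narrow and its practical effect small, and most of that stands.

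- **These patients are not lost to the trial.** A patient at ESRD remains at risk for the cardiovascular primary and contributes to secondary endpoints such as hospitalization days and femoral IMT. It would be wrong to say that the patient has already reached the trial's primary endpoint; that is true of the ESRD component only. Excluding such patients therefore costs cardiovascular information.
- **Few will enrol.** Recruitment is from a diabetes clinic, and the Abstract describes the target patients as at high risk of developing renal failure, which points to a population before ESRD. This is probably right, but it describes an intention that the entry rule does not enforce.
- **The article is condensed.** The definition of ESRD may sit in the full protocol, and its absence is not criticised here. The entry and exclusion criteria, however, are set out as lists, and the and/or wording is stated, not omitted.

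Three stronger readings are tempting, and the document does not support them.

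- A reader might infer that patients at ESRD would be counted as events in both arms and pull the relative risk towards 1. The endpoint is the development of ESRD, so disease present at entry is not an event.
- A reader might infer that every patient below 30 ml/min is uninformative. A patient below 30 who is not at ESRD can still decline and can still develop ESRD. For that patient the only issue is what the limit means.
- A reader might infer that the wider eGFR range undermines the sample size. The Sample size section calls 25 per group "adequate to estimate the mean of the eGFR between the two groups of participants" for a 2.5-unit difference. It gives no standard deviation and does not say whether the difference is in level, change or slope, so no such effect can be shown.

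**Conclusion.** The point holds as a mismatch between the entry rule and one component of the renal primary endpoint. As written, a proteinuric patient already at ESRD can be randomised although that patient cannot develop ESRD and has little or no eGFR decline to measure. Nothing elsewhere in the article repairs this.

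The expected effect is small. With one or two such patients per arm, the risk difference falls by 0.6 or 1.2 percentage points, the relative risk stays at 0.50, and its standard error on the log scale grows by about 3% to 5%. These figures rest on the assumed risks of 30% and 15%, on equal numbers in the two arms and on an assumed count. The true count is unknown and may be zero. The cardiovascular primary is not affected. This is a minor correction, worth making because it is cheap.

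**What to change.** Reconcile Eligibility criteria with Primary endpoints in one of two ways:

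1. Add an exclusion for patients who already meet the trial's own ESRD endpoint at randomisation. All 25 per arm are then at risk for the renal primary. The cost is one eligibility line and slightly fewer eligible patients.
2. If such patients are wanted for the cardiovascular primary, keep them and restrict the renal primary to patients free of ESRD at baseline. The restriction uses a characteristic fixed before randomisation, so the comparison stays randomised. The cost is slightly fewer patients in the renal analysis. Under the assumptions above it restores the 15-point difference but regains little precision. With 23 per arm the standard error is √(0.1449 + 0.2899 − 2/23) = 0.590, against 0.596 with the two patients kept in and 0.566 with 25 at risk.

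In either case the sponsor should state whether the limit of 30 ml/min is meant to apply to every entry route or to the eGFR route alone. Which is intended is for the sponsor and investigators to decide.

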### Allocation

Computer generated codes numbered 1–50 will be used to assign patients to either the intensive arm or the standard care arm. The randomization procedures are as follows:
The physician or nurse will explain to eligible patients about the international recommendation on performing regular follow-up to detect silent risk factors and complicationsThey will also explain to patients the need to assess the effectiveness of using a team to implement structured care by comparing the latter with usual careAfter the patient has signed the consent form, a study team member will open the envelope containing the randomization group and sign and date the envelopeThe signed envelope will be kept by the nurse in a secure place for audit purposesThe nurse will explain to the patient whether they have been randomized to the intensive arm or standard care arm and the assessment will proceed accordinglyThe nurse will keep a log of randomized patients and record status including study completion, premature discontinuation, withdrawal of consent or loss to follow-up

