### Statistical methods

Categorical data will be presented as frequency (percentage). Numerical data will be presented as mean (standard deviation (SD)), unless specified otherwise. Differences in baseline characteristics between two groups will be examined using the chi-square test or Fisher’s exact test for categorical variables and the two-sample *t* test or Mann-Whitney U test for continuous variables.

Logistic regression of binary outcomes such as cardiovascular events will be performed to determine the association between treatment group and potential risk factors and the outcomes. Relative risk (RR) (with 95% CI) will be calculatec. For continuous outcomes such as change in the MARS-5 and DDS17, linear regression will be used. Measure of tolerance for multicollinearity will be assessed. Coefficient B (with 95% CI) will be reported. The number of occurrences of hypoglycemia will be analyzed by Poisson regression. Measure of deviance will be checked and relative risk (RR) (with 95% CI) will be calculated.

*P* values < 0.05 will be deemed statistically significant. Statistical analysis will be performed using SPSS statistical software, version 19.0 (IBM Corp. Armonk, NY, USA). This RCT will be analyzed by the principle of intention to treat (ITT) and the per protocol (PP) approach.

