### Harms

Clinical observation and laboratory results will be used to evaluate the wellbeing of the patient on a continual basis throughout the duration of the study. In the event that the Investigator considers that the wellbeing of an individual patient is unacceptably at risk as a result of participation in the study then the individual patient will be withdrawn from the trial. In the event that the withdrawal of an individual also has wider implications for the wellbeing of other participating patients, then the study will be suspended and an investigation conducted to determine whether the trial should be continued as proposed, in a modified form or terminated.

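### Withdrawal is from the study, not only from the programme, so follow-up may stop for sicker patients and weaken the intention-to-treat analysis

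*Protocol article*

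**What the plan says.** The Eligibility criteria section lists the grounds for leaving under the sentence "Patients will be withdrawn from the study if any of the following criteria apply". Besides withdrawn consent and pregnancy, they cover a patient who can no longer take part and a patient whose participation the investigator ends for medical reasons after talking to the attending physicians. The same section adds: "There will be no participant replacement in the study if a participant withdraws".

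The Harms section deals with a patient whose wellbeing is judged unacceptably at risk because of taking part: "then the individual patient will be withdrawn from the trial".

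The Allocation section has the nurse keep a log of randomized patients and "record status including study completion, premature discontinuation, withdrawal of consent or loss to follow-up".

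The Primary endpoints section names a renal outcome (eGFR decline or worsening proteinuria, or "development of end-stage renal disease, whichever events happen") and a cardiovascular outcome ("composite events of acute myocardial infarction, revascularization procedures, heart failure, unstable angina, arrhythmia, stroke", transient ischaemic attack, and related death). The Abstract sets follow-up at 3 years. Under Statistical methods: "Logistic regression of binary outcomes such as cardiovascular events will be performed", and "This RCT will be analyzed by the principle of intention to treat (ITT) and the per protocol (PP) approach".

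**The concern.** Both withdrawal rules are mandatory, and both take the patient out of the study or trial, not out of the intervention. An intention-to-treat analysis needs outcomes for every randomized patient, whatever happens to their treatment. In patients with HbA1c of at least 9% and nephropathy, illness that prevents participation plausibly goes with a higher risk of end-stage renal disease, later cardiovascular events and death. If follow-up ends at withdrawal, those outcomes are missing for reasons related to the outcome.

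The loss may also differ by arm. The patient and the nurse know the allocation, and only the analysing statistician is described as blinded. The medical-grounds decision is discretionary. Patients in the intensive arm have nurse contact between visits, six social-worker sessions and self-monitoring tasks. Patients in the standard arm have 4-monthly visits and phone calls that they initiate themselves. Being unable to take part can therefore mean different things in the two arms, and be noticed at different times. With 25 patients per arm, a few such losses matter, and no later analysis can restore outcomes that were not collected.

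**Working it through.** **Setting the sections side by side**

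1. Eligibility criteria and Harms: the patient leaves the study or trial. Neither section mentions later outcome collection.
2. Allocation: the log distinguishes types of exit. It records status, not later outcomes.
3. Statistical methods: cardiovascular events are a binary outcome in a logistic regression, which makes no use of censored follow-up time. A patient withdrawn event-free at, say, month 14 has unknown 3-year status, and must be dropped, counted as event-free or imputed.

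**The plan's own figure**

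The article gives no withdrawal rate or event rate to reproduce. Its sample size (25 per group, 2.5-unit eGFR difference, two-sided alpha 0.05, power 0.80) comes without an SD. Inverting the t test gives a standardized difference of 0.809, so an implied SD of 2.5/0.809 = 3.09. With that SD, random loss of 20% (20 per arm) lowers power from 80% to 70.3%. That is ordinary attrition. It does not measure the bias at issue here.

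**Illustration A: a true effect, loss in one arm**

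Assumed 3-year risks: 30% control and 15% intensive. Expected events in 25 per arm: 7.5 and 3.75.

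- Full follow-up: RR = (3.75/25)/(7.5/25) = 0.150/0.300 = 0.50.
- Two control patients withdrawn before their events and dropped: RR = (3.75/25)/(5.5/23) = 0.150/0.239 = 0.63.
- The same two kept and counted as event-free: RR = (3.75/25)/(5.5/25) = 0.150/0.220 = 0.68.
- Two intensive-arm patients lost and dropped instead: RR = (1.75/23)/(7.5/25) = 0.076/0.300 = 0.25.

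The error goes either way, depending on which arm loses patients.

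**Illustration B: no true effect, loss in one arm**

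Let p be the true risk in both arms and s the share of would-be event patients in one arm who are withdrawn before the event. The observed risk among those retained in that arm is p(1 − s)/(1 − ps). Dividing by p gives the relative risk of that arm against the other: RR = (1 − s)/(1 − ps).

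| p | s = 25% | s = 50% |
|---|---|---|
| 10% | 0.75/0.975 = 0.77 | 0.50/0.95 = 0.53 |
| 20% | 0.75/0.95 = 0.79 | 0.50/0.90 = 0.56 |
| 30% | 0.75/0.925 = 0.81 | 0.50/0.85 = 0.59 |

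A 25% share is 25 × p × 0.25 = 0.6 to 1.9 patients, so fewer than two withdrawals. If s is the same in both arms, the relative risk stays at 1 and only events are lost.

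**The case against.** A reader might infer that the withdrawal rule contradicts intention to treat. The text does not support that. Intention to treat fixes who is analysed and in which arm. Nothing says that withdrawn patients leave the analysis set or lose data already collected, and they can be analysed as randomized with data up to withdrawal. Not replacing them is consistent with intention to treat.

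A reader might also infer that the rule removes patients heading for the primary events. No criterion names a renal or cardiovascular event, and consent withdrawal and pregnancy have no evident link to one. A stroke or heart failure that required admission before withdrawal would already count. What can be lost is an event, or further eGFR decline, after withdrawal. Amputation is not in the primary composite. The Harms rule covers only risk that results from taking part, so it does not reach patients whose disease simply worsens.

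The strongest objection is that the article condenses a fuller protocol, which may provide for follow-up after withdrawal. That limits the point but does not remove it: the published rule says that patients leave the study, which is more than silence about a detail. If the full protocol continues follow-up, the wording needs to be brought into line.

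Finally, both illustrations rest on assumed risks and on loss confined to one arm, neither of which is in the article. That objection stands in full, and is why no estimate of the actual bias is offered.

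**Conclusion.** The point holds in a limited form and should be acted on. As written, the withdrawal rules do not separate stopping the programme from ending outcome follow-up. They can therefore cause informative missing data in both primary endpoints, possibly differing by arm. This undermines the intention-to-treat analysis without formally contradicting it.

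This rests on two assumptions: that withdrawal from the study is applied literally, so that outcome collection stops, and that patients too ill to continue have a higher risk of later events. Illustrations A and B show only that, with 25 per arm, one or two withdrawals in one arm can move the relative risk materially. They do not predict how many will occur or in which arm.

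**What to change.** Reword the withdrawal text in the Eligibility criteria and Harms sections so that stopping the programme does not end outcome follow-up, and make it agree with Statistical methods. Unless the patient withdraws consent to data collection, collect eGFR, urine ACR, end-stage renal disease, cardiovascular events, hospital days and death to month 36 from routine clinic and hospital records. Analyse these in the allocated arm. The clinical decision to stop the programme is left as it is.

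The cost is a change to the protocol and consent-form wording and some record look-up, with no extra study visits. The burden should be small: the Data collection methods section already ties renal tests to endocrinologist reviews, and hospitalizations and deaths are already recorded as serious adverse events. The main limitation is that events treated at other hospitals may be captured incompletely.
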